## Abstract

**Background:**

Diabetes is a progressive condition requiring long-term medical care and self-management. The ineffective transition from hospital to community or home health care may result in poor glycemic control and increase the risk of serious diabetes-related complications. In China, the most common transitional care model is home visits or telephone interventions led by a single healthcare setting, with a lack of cooperation between specialists and primary care, which leads to inadequate service and discontinuous care. Thus, an integrated hospital-community-home (i-HCH) transitional care program was developed to promote hospital and community cooperation and provide comprehensive and continuous medical care for type 2 diabetes mellitus (T2DM) via mobile health (mHealth) technology.

**Methods:**

This protocol is for a multicenter randomized controlled trial in T2DM patients. Hospitalized patients diagnosed with T2DM who meet the eligibility criteria will be recruited. The patients will be randomly allocated to either the intervention or the control group and receive the i-HCH transitional care or usual transitional care intervention. The change in glycated hemoglobin is the primary outcome. Secondary outcome measures are blood pressure, lipids (total cholesterol, triglycerides, low-density lipoprotein, high-density lipoprotein), body mass index, self-management skills, quality of life, diabetes knowledge, transitional care satisfaction and the rate of readmission. The follow-up period of this study is six months.

**Discussion:**

The study will enhance the cooperation between local hospitals and communities for diabetes transitional care. Research on the effectiveness of diabetes outcomes will have potentially significant implications for chronic disease patients, family members, health caregivers and policymakers.

**Trial registration:**

Chinese Clinical Trial Registry ChiCTR1900023861: June 15, 2019.

## Background

Type 2 diabetes mellitus (T2DM) is a chronic metabolic disease that threatens human health and creates a large economic burden [1]. The ever-increasing prevalence of T2DM poses a severe burden to the health system [2, 3]. In China, T2DM affects 161.4 million people and contributes to 823,800 deaths. Diabetes-related costs reached 10.9 million USD in 2019, and they are expected to continue to grow [4]. Despite the health system's dedication to accelerating the development of chronic healthcare services, sufficient access for T2DM patients to health care and education has not been established [5, 6]. Diabetes awareness (36.5%), treatment (32.2%) and control (49.2%) rates are all at relatively low levels in China [7].

T2DM is a progressive condition that requires ongoing contact with medical settings and posthospital self-management to control blood glucose and reduce the risk of macro-microvascular complications and mortality [8, 9]. As inpatients transition from the hospital to the community and into the home, the increasing need for out-of-hospital patient care is crucial for healthcare organizations [10, 11]. Transitional care is generally recognized as an important aspect to ensure the quality of health care services and is widely used in chronic disease management. Transitional care incorporates a broad range of services designed to provide seamless care for patients as they move from one setting to another, and it has been proven to be effective in reducing unplanned admissions and mortality and improving care satisfaction [12–15].

Transitional care models are diverse in their health resources and local cultural characteristics [5]; they can be offered by teams or individuals [16, 17], include home visits or telephone coaching [18, 19], and be provided by the community or the hospital [20, 21]. The different forms have shown mixed results in terms of disease outcomes. The standard transitional care models for Chinese T2DM patients are relatively homogeneous and include home visits, telephone coaching and outpatient clinic [22, 23]. Patients passively obtain health information and lack access to interaction with their caregivers. And the content of health services is also limited in terms of health education, lacking methods and motivation for self-management and lifestyle change. In addition, T2DM patients need to travel between the hospital and the community for long-term medical services [24]. With separate operations in hospitals and communities in China, the transitional care team is usually led by a single care setting, leading to the interruption of services and health information [25]. A lack of solid collaboration between specialists and primary care introduces the potential for poor outcomes [15]. It is necessary to explore diverse access to health services and stratified care models to achieve continuous management, relationships, and information and effectively use community and medical resources.

Mobile health (mHealth), which refers to the delivery of health services via mobile devices such as wearable technology, smartphone applications (apps) and hand-held devices, has been rapidly developed and applied to numerous areas [26]. China has 986 million mobile internet users and a 70.4% internet penetration rate [27], and the vast internet market has increased the potential of mHealth to have considerable practical application for T2DM. Apps represent a valuable adjunct to provide low-cost and real-time ways to enable remote clinicians and personalized disease management and health information sharing [28]. The effectiveness and feasibility of app-related health care programs in T2DM management have been promising. These programs benefit self-management and quality of life in discharged patients with T2DM, aspects that should be promoted in community settings [29–33].

We designed a mHealth-based transitional care intervention that creates a support network with multiple agencies to establish a communication bridge between hospitals, communities and home healthcare providers. A professional diabetes-related app was developed to support a transitional care team providing continuous and remote health services for discharged patients. This paper describes the intervention protocol of a multicenter pragmatic randomized controlled trial (RCT) and hypothesizes that it will promote T2DM patients' glycemic control, self-management skills and other health outcomes. Our primary outcome is the change in glycated hemoglobin (HbA_1c_) at the 6-month follow-up; other outcomes are described below.

## Methods

### Study objective

The primary goal of this study is to assess whether the mHealth-based i-HCH transitional care program, by facilitating hospital-community collaboration and ensuring that patients receive continuity of care in the transition from hospital to the community or home with the use of mHealth technology, reduces T2DM patients' HbA_1c_ values compared to usual transitional care. The secondary goals are to (1) remotely monitor and dynamically assess risk factors for T2DM patients, implement personalized health interventions and education for patients to change poor health behaviors, improve patients' self-management skills and disease knowledge, and improve patients' lipid, blood pressure and body mass index (BMI) profiles; (2) through comprehensive interventions resulting in the overall improvement in patient quality of life, satisfaction with care, and reduction in patient readmissions; and (3) to understand the feasibility and applicability of the alliance between specialists in primary care in the clinical environment.

### Study design

This study is a multicenter pragmatic RCT with a 6-month follow-up period performed at a large general hospital and in 8 communities in Shanghai, China. The study will be conducted with a transitional care team that includes clinical nurses certified in diabetes care, physicians, endocrinologists, community nurses (CNs), general practitioners (GPs), pharmacists and administrative support staff to begin mHealth-based integrated hospital-community-home (i-HCH) transitional care to facilitate the glycemic control of discharged patients with T2DM and guide their self-management skills. Patients who meet the eligibility criteria will be included and randomized to receive the i-HCH transitional care or usual transitional care intervention. The allocation ratio will be 1:1. Due to the characteristics of the study, trial team members and participants will not be blinded, while the data collectors and statistical analysis assistants will be blinded.

### Participant recruitment and randomization

Patients admitted to the Department of Endocrinology in a large general hospital will be screened for eligibility based on electronic medical record data. The study eligibility criteria are as follows: (1) the participant is aged between 18 and 70 years old; (2) the participants' most recent HbA_1c_ ≥ 7.0% (53 mmol/mol); (3) the participant can use smartphones and apps; (4) the participant will return home and reside around the eight target communities; and (5) the participant can communicate and read in Chinese. The ineligibility criteria are as follows: (1) having type 1 or gestational diabetes; (2) lacking reliable internet access (no access to 4G,5G, or Wi-Fi connection); (3) being homeless or living in other care centers; (4) having debilitating complex medical conditions, e.g., end-stage cancer, dialysis, severe mental illness; and (5) refusal to sign an informed consent form or fall by the wayside.

Clinical nurses will explain the objective and procedure of the study face-to-face and give candidates a program booklet. If the patient participates, they will be formally referred to the study and provided informed consent. Then, the patients will be allocated to the intervention or control group using a random number generator programmed in SPSS (IBM Corp, version 23.0, Chicago, IL, USA).

### Study outcomes

The change in HbA_1c_ is the primary outcome. The secondary outcome measures are as follows: (1) clinical outcomes, including blood pressure, lipids (total cholesterol [TC], triglycerides [TGs], low-density lipoprotein [LDL], high-density lipoprotein [HDL]), and body mass index (BMI); (2) diabetes self-management skills assessed using the Summary of Diabetes Self-care Activities questionnaire (SDSCA) [34]; (3) quality of life using the Diabetes-Specific Quality of Life scale (DSQL) [35]; (4) diabetes knowledge using the Diabetes Knowledge Test (DKT) [36]; (5) transitional care satisfaction; and (6) the rate of readmission.

### Data collection

Participants' baseline data will be collected three days before discharge, and a questionnaire regarding demographics will be completed. Data collection will be conducted at 3 and 6 months after discharge. Patients will attend clinical appointments in the study hospital or designated community hospitals to complete clinical and laboratory assessments. Research assistants will upload the results to the diabetes management platform for secure collection. The research assistant will collect the questionnaires face-to-face during the outpatient visit. The patients' blood glucose data and hypoglycemia events will be supervised and consulted by CNs through the app or telephone. Readmission will be determined by referring to the participant's medical history in the general hospital. All data will be double-entered and checked for consistency. The study flowchart and participant data collection are depicted in Fig. 1 and Table 1.

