Team members will transmit educational articles on the app weekly to patients and their families to help them learn about diabetes, such as hypoglycemia and signs of exacerbation. The pharmacist will provide professional pharmaceutical knowledge, such as skills on taking medication correctly, the importance of medication adherence and ways to adjust the insulin dose.

CNs will note app usage and self-care status and present health information for discussion in monthly team meetings. The intervention strategy will be adjusted accordingly to meet patients' needs when member consensus is achieved. Then, routine endocrinologist appointments will be performed in the third and sixth months after discharge. The app will send follow-up reminders to patients and provide information on the critical content and a preparation list two weeks before follow-up. Patients will be immediately recommended to schedule urgent appointments and will be referred to the general hospital with the responsible endocrinologist if they have unsafe glycemic levels or develop acute or chronic diabetic complications.

In the control group, participants will receive usual transitional care alone. Participants who achieve stable blood glucose are usually discharged with an in-home management plan drawn up by clinical nurses and physicians. Outpatients will attend regular clinic visits at the general hospital, with an interval of approximately three months. Participants can access health care from community hospitals in-between clinic visits if needed. The clinical nurses will perform a consultation to assess the outpatient's self-management condition once every three months and obtain blood glucose data that patients provide via a paper record or from a commercial glucose meter over the telephone or during a home visit; in addition, the clinical nurses will provide general advice and renew the diabetes management plan.

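### Readmission is ascertained from one hospital's records only, so admissions elsewhere are missed, and capture may differ by arm in a direction the documents do not settle

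*Protocol article*

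**What the plan says.** Study outcomes lists readmission last among the secondary outcomes ("6) the rate of readmission"), and Study objective makes fewer readmissions part of a secondary goal. Data collection fixes how it is measured: "Readmission will be determined by referring to the participant's medical history in the general hospital". No other source is named for this outcome.

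The setting is wider than that hospital. Study design says the trial is "performed at a large general hospital and in 8 communities in Shanghai, China", and Data collection allows follow-up assessments at the study hospital or at designated community hospitals.

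The care pathways, mostly in Study intervention, differ by arm:

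- Intervention: when glucose values are dangerous or complications of diabetes appear, the rule is "Patients will be immediately recommended to schedule urgent appointments and will be referred to the general hospital with the responsible endocrinologist". The app is also linked to the hospital's outpatient booking (Description of the diabetes management system). Day-to-day monitoring and consultations lie with community nurses and GPs, and endocrinologist appointments follow in months 3 and 6.
- Control: "Outpatients will attend regular clinic visits at the general hospital, with an interval of approximately three months". In addition, "Participants can access health care from community hospitals in-between clinic visits if needed". Clinical nurses assess self-management every three months. No referral rule like that of the intervention arm is described.

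**The concern.** An outcome meant to show whether integrated care keeps patients out of hospital is read from one institution's history. Two problems follow.

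First, admissions to a community hospital or to another general hospital do not enter the count, so the rate in each arm is understated by the share of admissions that happen elsewhere.

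Second, the intervention is designed to change how patients reach the hospital and the community services. If that also shifts where they are admitted, the share captured differs by arm, and the comparison mixes the effect on readmission with an effect on place of admission. A null result, a benefit or an apparent harm could each partly reflect the latter, and the data as planned could not tell them apart.

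**Working it through.** **The plan's own figures.** The article gives no readmission rate, no target difference and no capture share. The only number needed from it is the group size. For HbA1c (difference 0.5, SD 1, two-sided alpha 0.05, power 0.8), n per arm = 2 × (1.960 + 0.842)² × 1² / 0.5² = 62.8, so 63, or 126 in total, as stated. Adding 10% gives 63 × 1.1 = 69.3, which matches the stated 69 per group. This calculation is not at issue; 69 per group is used below.

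**Formulas.** Let p be the true readmission risk and c the share of readmissions that occur at the general hospital and so are captured.

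- Observed risk = p × c.
- Observed risk ratio (RR) = true RR × (c in intervention / c in control).
- Power = Φ{[|p₁ − p₂| − 1.96 √(2p̄(1 − p̄)/n)] / √([p₁(1 − p₁) + p₂(1 − p₂)]/n)}, with p₁ and p₂ the observed risks, p̄ their mean and n = 69.

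**Results.** All true risks and capture shares are assumptions. Capture is given as intervention/control; risks are intervention v control.

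| Capture | Observed, true 20% v 20% | RR | Observed, true 10% v 20% | RR | Power |
|---|---|---|---|---|---|
| 100%/100% | 20% v 20% | 1.00 | 10% v 20% | 0.50 | 0.375 |
| 70%/70% | 14% v 14% | 1.00 | 7% v 14% | 0.50 | 0.267 |
| 95%/80% | 19% v 16% | 1.19 | 9.5% v 16% | 0.59 | 0.206 |
| 95%/75% | 19% v 15% | 1.27 | 9.5% v 15% | 0.63 | 0.164 |
| 90%/70% | 18% v 14% | 1.29 | 9% v 14% | 0.64 | 0.149 |
| 70%/90% | 14% v 18% | 0.78 | 7% v 18% | 0.39 | 0.497 |

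The RR under equal true risks depends only on the ratio of the two capture shares (0.95/0.80 = 1.19; 0.95/0.75 = 1.27; 0.70/0.90 = 0.78), not on the 20% chosen.

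**Reading.** Equal incomplete capture lowers the rates and the power but leaves the RR intact. Lower capture in controls pushes the RR up, against the intervention. Lower capture in the intervention arm pushes it down and overstates the benefit; the 0.497 in the last row is the chance of a significant result for an exaggerated effect, not a gain in power.

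**Can the direction be read from the text?** The intervention arm's referral rule and booking link point towards the general hospital, and the control arm's use of community hospitals points away from it. Against that, controls attend the general hospital about every three months, while intervention patients are managed from day to day by community staff. Both the referral and the booking link concern appointments, not admissions. The text supports no sign for the difference.

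**The case against.** A reader might infer that controls lose more readmissions than intervention patients, and hence that the trial is biased against its own intervention. The documents do not support that. The referral is for urgent appointments, the app books outpatient visits, and neither says where a patient is admitted. Nothing states that the community hospitals admit inpatients. Both arms have specialist contact about every three months. Differential capture could be nil or reversed. This part of the objection stands in full.

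A reader might also infer that the outcome cannot be interpreted at all. That goes too far. Every participant is recruited from this hospital's endocrinology department, the same record rule applies in both arms, and data collectors are blinded. Readmission to the index hospital is a coherent outcome if it is labelled so, and with equal capture its risk ratio is unbiased.

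Two further arguments carry less weight. A medical history might include admissions elsewhere that the patient reports, but the text does not say so. And although an article leaves detail to the full protocol, this point concerns a source the article names, not a definition it omits. Blinding does not help either: a blinded collector cannot find an event that is absent from the source. The Discussion's remark that patients are usually seen in general hospitals is not specific to the study hospital.

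**Conclusion.** The point holds in limited form. As stated, the rule misses readmissions to any hospital other than the general hospital, for an outcome tied to a stated goal of the trial. Confidence in incomplete capture is high, provided that some admissions occur elsewhere and that the history does not record them. That capture differs by arm is a possibility only, of unknown size and direction.

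Across the assumed cases, a true risk ratio of 1.0 would be observed as anything from 0.78 to 1.29, and as exactly 1.0 if capture is equal. These figures show sensitivity; they are not estimates. The HbA1c primary outcome is untouched. Severity is minor to moderate: a secondary outcome with a real ascertainment gap and a cheap remedy.

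**What to change.** - Define the outcome as admission to any hospital within six months of discharge.
- Have the blinded data collectors ask one identical question about admissions anywhere, in both arms, at the existing 3- and 6-month face-to-face questionnaires.
- Confirm reported events with discharge papers or hospital records. Where available, check the participating community hospitals' records for all participants, not only for those who report an event; this also covers anyone who misses a visit.
- Report the general-hospital-only count as a sensitivity analysis, labelled same-hospital readmission.

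The cost is one question at two planned contacts plus the record checks. No new visit is needed and clinical management does not change. The drawback is recall error over about three months and possible arm-dependent reporting, because participants are not blinded. Record confirmation limits both, but it cannot recover an unreported admission to a hospital whose records are not checked.

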**Fig. 1 Fig1:**
[figure not shown]
Study flowchart: participants' recruitment, randomization and follow-up

**Table 1 Tab1:**
[figure not shown]
Summarize the schedule of enrolment, interventions, and assessments

### Description of the diabetes management system

The system comprises a patient app, a medical app and a management portal. In partnership with the mHealth Industrial Research Organization, the Department of Internet Information and Endocrinology at the General Hospital, and the community hospitals, we developed an app to address the integrated transitional care of T2DM patients. The app is user-friendly and modeled on a complete general hospital patient management platform that supports remote patient management.

The app can display various health records and the patients' physiological, biochemical, imaging examination, and hospitalization history data. With the patients' consent, the patients' family and transitional care term members can review relevant data on their mobile phones. The patient can manually enter the blood glucose value, blood pressure and body weight on the app, generating a dynamic curve. If these values exceed the target set by physicians, they will be marked in a significant color to alert the patient. Patients can check the frequency and dosage of oral medications and insulin in their recent prescriptions and record whether they have taken them through the app. The app can generate an individualized alarm clock that reminds patients to take their medications. In addition, the app supports recording daily food, physical activity and diabetes-related stress. The app automatically stratifies patients into three subgroups based on their blood glucose level and the frequency of health recordings and displays the subgroup on the medical app home page. The three patient subgroups include the following: warning patients with severe high or low blood glucose values (> 13.9 mmol/L or < 3.9 mmol/L); key patients with blood glucose values that exceed the target value or have no health recordings within a two-week time period; and general patients.

The app has a diabetes knowledge base from which patients and their families can read diabetes-related articles. The app is connected to the hospital outpatient system to conveniently allow patients to book outpatient appointments while updating the follow-up time and results. Its counseling function allows patients to actively communicate with the transitional care team when encountering adverse reactions or acute changes in their diabetes condition to seek professional help. Patient data will be regularly transmitted and uploaded to the management portal via the internet and subsequently presented in tabular or graphical formats for team members to oversee the patients' condition. We assessed clinician and patient demand for the diabetes app through a qualitative study and feasibility test (n = 17) to enhance the platform. This system will be utilized in this RCT.

